**Figure 1 F1:**
[figure not shown]
**Trial design flowchart**. Trial design.

### Programming requirements

The objective of the programming requirements for the PREFER trial is to detect AF (as inferred by atrial high rate episodes), and/or ventricular high rates for either AF with rapid ventricular response rate or ventricular tachycardia. Specific requirements are listed in Table 1.

**Table 1 T1:** Programming requirements

**Parameter**	**Value**
Atrial high rate episode	Rolling
Ventricular high rate episode	Rolling
Ventricular minimum detection duration rate	5 beats

### Data collection

All scheduled and unscheduled transmissions will be recorded. Designated physicians and nurses at the clinical site will determine if a clinically actionable event can be diagnosed based on the transmitted data. Additional information will be collected at each office visit, including medication changes and the performance of device interrogations. The data collected and stored during interrogations consists of an evaluation of thresholds, lead impedance, battery voltage, as well as a review of device diagnostics, and stored electrograms.

### Statistical methods and data analysis

#### Sample size methods and assumptions

Data from the Atrial High Rate (A-HIRATE) study were used to estimate the survival rates for patients in each arm of the PREFER trial. The A-HIRATE study evaluated pacemaker patients implanted with a Kappa 700 or Kappa 900 device [8]. Due to device diagnostic limitations of the Kappa 700, only the 157 subjects in the A-HIRATE study that were implanted with a Kappa 900 device and followed through at least one month post-implant were used for event rate estimation, as this most closely approximates patients in the PREFER trial.

Simulations were used to determine the sample size necessary to evaluate the primary objective while following patients through quarterly remote interrogations compared to the combination of TTM transmissions and in-office visits, while achieving 80 percent power and α = 0.05. A sample size requirement of 700 subjects was determined.

#### Analysis of primary objective

The time to first diagnosis of a clinically actionable event or censoring will be determined for each randomized subject. The Peto & Peto modification of the Gehan-Wilcoxon test will be performed [9]. Only events diagnosed by the clinician will count toward the primary endpoint. If the test yields a p-value less than 0.05, it will be concluded that the freedom from first diagnosis of clinically actionable event(s) is significantly lower when patients are followed through remote interrogation as they were in this trial, compared to being followed through TTM and scheduled in-office visits.

#### Analysis of secondary objectives

The same analysis will be repeated for each of the individual events that make up the composite primary endpoint. In addition, actions taken in response to the clinician awareness of these events will be summarized.

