**Methods:**

The **P**acemaker **RE**mote **F**ollow-up **E**valuation and **R**eview (PREFER) trial is a prospective, randomized, parallel, unblinded, multicenter, open label clinical trial to determine the utility of remote pacemaker interrogation in the earlier diagnosis of clinically actionable events compared to the existing practice of transtelephonic monitoring. There have been 980 patients enrolled and randomized to receive pacemaker follow up with either remote interrogation using the Medtronic CareLink^® ^Network (CareLink) versus the conventional method of transtelephonic monitoring (TTM) in addition to periodic in-person interrogation and programming evaluations. The purpose of this manuscript is to describe the design of the PREFER trial. The results, to be presented separately, will characterize the number of clinically actionable events as a result of pacemaker follow-up using remote interrogation instead of TTM.

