### Primary endpoint

The primary endpoint is the rate of first diagnosis of clinically actionable events in patients whose pacemakers are followed by remote interrogation versus those whose pacemakers are followed by office visits augmented by TTM. The goal of early identification of clinically actionable events is to have early intervention by a clinician, which could impact the clinical sequelae. The clinically actionable events were selected on the basis that their presence merits a clinical decision or further medical assessment. Clinically actionable events are defined as:

• Atrial tachycardia (AT)/AF episodes ≥ 48 hours (defined as two consecutive days in which the device records at least 18 hours of AT/AF per day)

• Ventricular pacing that has increased by 30 percent relative since last device interrogation

• Sensed ventricular rate of ≥ 100 bpm during atrial arrhythmia for at least 20 percent of the time since previous device interrogation

• Non-sustained ventricular tachycardia (NSVT) ≥ 5 beats

• New onset AT/AF in patients with no prior history of AT/AF

• Loss of capture

• Increase in pacing voltage threshold ≥ 1 V

• Significant changes in atrial or ventricular lead impedance, defined as:

◦ < 200 of > 2000 ohms

◦ Unstable lead impedance deemed to be clinically actionable

◦ ≥ 50 percent change in lead impedance since last interrogation

• Elective Replacement Indicator (ERI) or End of Life (EOL)

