### Design

The PREFER trial is a prospective, randomized, parallel, unblinded, multicenter, open label clinical trial to investigate the clinical value of remote interrogation in the management of patients with pacemakers. All study patients received a Medtronic Kappa^® ^900, EnPulse^®^, Adapta™, or Versa™ device supported by CareLink. The pacemakers are either single- or dual-chamber devices. Fifty investigative centers in the United States (US) enrolled a total of 980 patients between May 2004 and March 2007, with planned 12-month follow up.

The primary inclusion criteria are:

◦ Patient is at least 30 days post system modification, including new device implant, device upgrade, or lead changes.

◦ Patient has access to an analog phone line.

◦ Patient is capable of operating the TTM monitor and the CareLink Monitor.

The exclusion criteria are:

◦ Enrollment in another pacemaker clinical study that might confound the results of this trial.

◦ Patient is a candidate for an ICD.

All patients who met eligibility requirements and signed an Institutional Review Board (IRB) approved PREFER trial Informed Consent Form and an Authorization for the Use and Disclosure of Health Information underwent an in-office baseline evaluation to quantify baseline characteristics. Baseline evaluations included pacemaker information, cardiovascular medical and surgical history, New York Heart Association (NYHA) classification, and arrhythmia history.

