### Randomization

Patients were randomized 2:1 to remote interrogation at three month intervals or TTM evaluations at two month intervals. A permutated block randomization was used to randomize the subjects. Patients who were randomized to follow up with the remote interrogation will transmit pacemaker information at 3, 6, and 9 months after enrollment and have an office visit at 12 months post-enrollment. The TTM control subjects with single chamber devices will transmit 30 second TTM strips with and without magnet application at 2, 4, 6, 8, and 10 months after enrollment and have an office visit at 12 months. Patients with dual chamber devices will transmit via TTM at 2, 4, 8, and 10 months after enrollment, with office visits at 6 and 12 months post enrollment. The frequency of TTM transmissions is the maximal permitted under Centers for Medicare and Medicaid Services (CMS) reimbursement guidelines [7] and reflective of average frequency of TTM transmissions from Medicare patients. The trial design flowchart is shown in Figure 1.

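### Read literally, the new-onset AT/AF component is tested in all randomized patients, including those whose AT/AF history means they cannot have the event; this dilutes its incidence and absolute arm difference and costs some power

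*Protocol article*

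**What the plan says.** All statements are in the protocol article.

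- **Primary endpoint** lists the clinically actionable events. One of them is "New onset AT/AF in patients with no prior history of AT/AF".
- **Analysis of primary objective** sets the analysis population: a time to diagnosis or censoring "will be determined for each randomized subject". The test is the Peto-Peto version of the Gehan-Wilcoxon test.
- **Analysis of secondary objectives** carries this over to the components: "The same analysis will be repeated for each of the individual events that make up the composite primary endpoint". It names no subset for any component.
- **Design** does not list prior AT/AF among the exclusions. The baseline evaluation records "New York Heart Association (NYHA) classification, and arrhythmia history", so a patient's AT/AF history is available.
- **Secondary endpoints** says that the component objectives assess what each event contributes to the primary objective.

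**The concern.** The stated population does not fit one of the events to which it is applied. A patient with prior AT/AF cannot, by definition, have new-onset AT/AF. In the literal analysis that patient stays in the risk set until censoring and is counted as free of the event throughout.

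Two things follow for this component. The freedom-from-event curve lies above the curve for patients who could have the event, and a reader may take it for the new-onset rate in patients without AT/AF. The test also becomes less sensitive. Peto-Peto weights follow the pooled survival estimate, so patients who can never have the event hold the weights nearer to 1. The remote arm gains by diagnosing early and the control arm catches up at its office visits; with flatter weights that later catch-up is discounted less.

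**Working it through.** **The plan's own figure.** The only sample-size result is "A sample size requirement of 700 subjects was determined", obtained by simulation "while achieving 80 percent power and α = 0.05". It belongs to the composite. The simulated survival rates per arm are not printed, so it can be neither reproduced nor refuted, and nothing below depends on it.

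**Inputs from the article**
- Patients: "There have been 980 patients enrolled and randomized", allocated 2:1, so about 653 remote and 327 control.
- Full interrogations: remote at 3, 6, 9 and 12 months; dual-chamber control at 6 and 12 months (Randomization).
- Event rate, for illustration: in A-HIRATE, 46% of patients without AF history had at least one atrial high rate episode by 24 months (Discussion).

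**Assumptions**
- The share with prior AT/AF, q, is not given; 20%, 40% and 60% are used.
- Constant hazard, and the 46% taken as a stand-in for clinician-diagnosed new onset.
- All controls follow the dual-chamber schedule, unless stated otherwise.

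**Step 1: risk among patients who can have the event**
- Hazard = −ln(1 − 0.46)/24 = 0.0257 per month.
- 12-month risk = 1 − 0.54^0.5 = 26.5%.
- Diagnosed by month 9 with perfect detection: remote has found onsets up to month 9, 1 − exp(−9 × 0.0257) = 20.6%. Control has found onsets up to month 6, 1 − exp(−6 × 0.0257) = 14.3%. The difference is 6.4 points (from unrounded values) and the ratio 1.45.

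**Step 2: the same quantities in all randomized patients**

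Risk in all = (1 − q) × risk in those at risk. Randomization makes q equal between arms in expectation, so the factor cancels from the ratio but not from the difference.

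| Population | 12-month incidence | 9-month remote | 9-month control | Difference (points) | Ratio |
|---|---|---|---|---|---|
| At risk only | 26.5% | 20.6% | 14.3% | 6.4 | 1.45 |
| All, q = 20% | 21.2% | 16.5% | 11.4% | 5.1 | 1.45 |
| All, q = 40% | 15.9% | 12.4% | 8.6% | 3.8 | 1.45 |
| All, q = 60% | 10.6% | 8.3% | 5.7% | 2.5 | 1.45 |

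**Step 3: the Peto-Peto test, by simulation at 980 patients, 2:1**

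Mean Z, all randomized against at-risk only:

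| q | 70% detection per interrogation, about 10% yearly censoring | Fall | Perfect detection, no dropout | Fall |
|---|---|---|---|---|
| 20% | 1.19 v 1.31 | 9% | 0.61 v 0.77 | 21% |
| 40% | 0.99 v 1.22 | 19% | 0.33 v 0.60 | 45% |
| 60% | 0.70 v 0.97 | 28% | 0.21 v 0.55 | 62% |

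The imperfect-detection columns rest on 600 trials per setting. A separate run of 1,500 gave 1.13 v 1.26, 0.90 v 1.12 and 0.67 v 0.93, which are falls of 10%, 20% and 28%. The perfect-detection columns rest on 1,500 trials.

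Power in the 600-trial runs (share with Z above 1.96), all randomized against at-risk only, was 21% v 26%, 16% v 21% and 9% v 14% at q = 20, 40 and 60%. With 15% single-chamber devices (assumed), q = 40%, 70% detection and dropout, it was 17% v 24% (800 trials). Under perfect detection with q of 30–60% it was 5–7% v 7–9%.

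A simple two-proportion comparison at 9 months loses less: 56% v 58%, 43% v 46% and 29% v 32% at the same three values of q.

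**The case against.** **The all-randomized reading is inferred.** The event's own definition names the patients concerned, and the reference to each randomized subject is written for the composite, for which everyone is at risk. The full protocol or SAP, not shown here, may set the component's risk set. This stands as a limit on confidence. It does not remove the point, because the article does state a population and then says that the same analysis is repeated.

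**All randomized patients are a legitimate denominator for contribution to the composite.** This also stands. A reader might infer that the diluted curve describes no real population. Given the purpose in Secondary endpoints, that goes too far: it describes how often follow-up yields this diagnosis among all randomized pacemaker patients. It is not, however, the new-onset rate among patients who can have the event, and it gives the weaker test.

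**The comparison is not biased.** Correct. A reader might infer a distorted treatment comparison or a false-positive risk. History is balanced in expectation, the ratio stays at 1.45, and dilution does not inflate the type I error.

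**The size is uncertain and the test is weak anyway.** Largely right. A reader might take a 40–60% fall in Z as the general result, but that needs perfect detection and q of about 40% or more. Power for this component is low under either population, so the main consequence is the reported incidence and absolute difference. The 46% is any device-recorded episode in another study, not a clinician's diagnosis in this one.

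**Conclusion.** The point holds for one secondary component, on the literal wording. The factor (1 − q) on incidence and on the absolute difference is exact in expectation; its value is unknown because q is not given. Restriction to patients at risk gave the larger mean Z in every setting tried. How much larger depends on q and on the assumed detection rate, from roughly 10% to about 60%.

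The primary composite does not change, since patients with prior AT/AF can have its other events. The risk ratio, the type I error and the sample size of 700 are also untouched. This is a free improvement, not a threat to the trial's main conclusion.

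**What to change.** Add to Analysis of secondary objectives: *For new-onset AT/AF, the time-to-first-diagnosis test and curve use only randomized patients with no AT/AF history at the baseline evaluation; the number at risk is reported per arm. The count of these diagnoses among all randomized patients is also given, to describe the contribution to the composite.*

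The cost is one sentence. It uses a baseline variable already collected, so the randomized comparison is preserved. No event is lost, because the patients left out cannot have this one. The sentence should be in place before the component is compared by arm.

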#### Supplemental analyses

Subsequent to verification of database accuracy and closure, an examination of the distribution of each study endpoint will be performed. Descriptive statistics for each demographic variable will be calculated which include measures of average, variability, frequency, and a count of the number of missing values. No data imputation will be performed. When the mean is found not to be an appropriate measure of central tendency, alternative statistics will be considered (e.g. median).

The distribution of demographic and clinical background parameters will be summarized for the study population overall and for each relevant study group.

Subjects in the remote interrogation arm of the trial will be asked to complete a patient survey at the 12 month visit in order to characterize the burden of in-office follow-up assumed by patients and their family. The survey questions include mileage traveled and time spent by the patient to reach the office, type of transportation used, necessity of the patient to take time off of work for the office appointment, and time spent by any family members in order to bring patient to the office. Descriptive statistics will be computed to summarize the results of the questionnaire.

## Discussion

The PREFER trial hypothesized that the systematic remote interrogation allows clinicians earlier and more complete access to pacemaker diagnostic data than TTM and scheduled in-office visits. If the results support this hypothesis, events such as ventricular response rate in AF, presence of NSVT, rising lead thresholds, and significant changes in lead integrity and battery status, will therefore be detected earlier so that earlier clinical actions and decisions may then take place. Thus, the pacemaker monitoring system can become much more a part of clinical decision and management.

One of the most common arrhythmias encountered in pacemaker patients is AF. In a study by Gillis et al of incidence of AF in pacemaker patients, 15 percent of patients who developed AF as documented on their pacemakers did not have AF pre-implant [10]. In the A-HIRATE trial, 46 percent of patients without a history of AF developed at least one atrial high rate episode (AHRE) by 24 months [8]. Because symptoms are often inaccurate [11] and patients are frequently asymptomatic in AF, earlier identification of AF by pacemakers, with frequent access to the data via remote monitors, can mean earlier initiation of appropriate anticoagulation which may reduce stroke events.

The relationship of AF burden to stroke risks remains unclear. In an ancillary study from the MOde Selection Trial (MOST), patients with atrial high rate episodes (AHRE) greater than 5 minutes had twice the death and stroke rates as patients without any AHRE [2]. In another study, patients with AHRE greater than 1 day had a 3-fold increase in strokes compared with patients with AHRE less than a day [12]. The continuous monitoring capabilities of pacemakers may assist in determining exactly the association between the amount of AF burden and stroke rates. The TRENDS study, which aimed to study the relationship between duration of AHRE and stroke events in patients with AF and who are not anticoagulated, has completed enrollment and is currently in analysis phase, and will be providing more data [13]. The ASSERT study is also underway and will evaluate whether the detection of AHRE with pacemaker telemetry predicts an increased risk of stroke and other vascular events [14]. If a relationship does exist between the duration of AF and stroke risks, then the ability to diagnose AF as soon as possible via a remote monitoring system could indeed be a clinically valuable tool.

Other advantages of remote monitoring of pacemakers include the ability to access rate histograms. In patients with known AF, rate control is crucial to avoid tachycardia-mediated cardiomyopathy, and frequent remote access to rate histograms can allow clinicians to better monitor the success of rate control. Additionally, the potential detrimental effects of right ventricular pacing have gained prominence in recent years. A substudy from MOST demonstrated an increased risk of heart failure hospitalization in patients who had over 40 percent ventricular pacing [15]. The incidence of AF also increased with right ventricular (RV) pacing. Pacemakers now document the percentage of RV pacing delivered, thus allowing clinicians to make programming changes to limit the amount of RV pacing. Ventricular high rate episodes recorded by pacemaker may also suggest NSVT, which may be an indication of cardiomyopathy in patients not previously suspected to have structural heart disease. Appropriate screening can then be performed to assess the patients' risks for sudden cardiac death and candidacy for upgrade to an ICD.

Remote monitoring systems are in widespread use for monitoring ICDs, but have not yet been studied for the monitoring of pacemakers. To our knowledge, this is the first large, multi-centered trial to compare the utility of remote monitoring systems with the existing system of TTM and office visits. It is our hypothesis that pacemaker patients can develop clinically significant arrhythmic issues, that pacemaker diagnostic data are sophisticated and numerous, and that frequent access to these data via remote monitoring can result in earlier actions by clinicians.
